## Measures

Outcome measures are brief, to minimize assessment fatigue. The assessment schedule is provided in Table 1.

**Table 1 T1:** Assessment schedule

**Measures**	**Timepoint**					
	**Recruitment**		**Follow ups**			
**(Timeframe)**	**Screen**	**Baseline**	**1 Mth**	**3 Mth**	**6 Mth**	**12 Mth**
	**(-t1)**	**(-t1)**	**(t1)**	**(t2)**	**(t3)**	**(t4)**
Demographics	X			X	X	X
Alcohol use disorders identification test (AUDIT)	X (3 mths)		X (1 mth)	X (3 mths)	X (3 mths)	X (3 mths)
Substance use risk profile scale (SURPS)		X			X	X
Timeline followback (TLFB; 1 mth)	X (2 wks)	X	X	X	X	X
Controlled drinking self-efficacy scale (CDSE; 3 mths)		X		X	X	X
Rutgers alcohol problem index (RAPI; 3 mths)		X	X (1 mth)	X	X	X
Alcohol trivia		X	X			X
University of Rhode Island Change Assessment Scale (URICA; current)		X	X	X	X	X
Extended-adolescent injury checklist (E-AIC; 6 mths)		X			X	X
Mental health: Kessler 10 (1 mth), Generalised Anxiety Disorder-7 (GAD-7; 2 wks), Mini Social Phobia Inventory (Mini-Spin; 1 wk); Patient Health Questionnaire-9 (PHQ-9; 2 wks)		X	X	X	X	X
Coping in stressful situations (CISS)		X		X	X	X
Social & role functioning (1 mth)		X	X	X	X	X
Client satisfaction questionnaire (CSQ-8)			X			
Other treatment service use			X	X	X	X
Assessment of quality of life-6D (AQoL-6D)		X		X	X	X

Note. mth: month; wk: week.

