### Screening measures

(i) Demographics: age, gender, occupation, years of education, living arrangements, relationship status, ethnicity.

(ii) Alcohol use: A 2-week *TLFB* uses calendar-based cues to obtain precise information on the frequency and quantity of alcohol use [58]. The 10-item *AUDIT* screens participants for harmful or problematic drinking in the previous 12 months. This well validated measure reliably detects alcohol use disorders in adolescents and adults at a cut-off of ≥ 8 [53].

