### Baseline and follow-up measures

(i) Personality risk: The *Substance Use Risk Profile Scale* (SURPS) [60] is a 23-item measure of the level of anxiety sensitivity/proneness (5-items), depression proneness/hopelessness (7-items), impulsivity (5-items), and sensation seeking (6-items) personality risk factors for alcohol abuse or dependence. This scale has high levels of internal consistency, test-retest reliability and construct, concurrent and predictive validity with respect to current and future alcohol use in adolescents, undergraduate students and clinical samples [30,60,61]. It also has high levels of incremental validity (cf. other personality measures) for differentiating reinforcement-specific patterns of drug use [29,60].

(ii) Alcohol and other drug use: *TLFBs* over the previous 4 weeks assess the frequency and quantity of alcohol and other substance use across the study [58]. The *TLFB* method has high test-retest reliability (intraclass correlation coefficients (ICC) = .70-.94), convergent and discriminant validity with other substance use measures, collateral information and biological measures of illicit drug use [58,62]. We found substantial agreement between urine drug screens and self-reported drug use (83%) using the TLFB in a previous study [63]. The age of onset and frequency of alcohol and other drugs use over the previous 12 months is also assessed at baseline.

(iii) Other alcohol outcome measures. Alcohol-related knowledge is assessed using 20 *Alcohol Trivia* questions developed for this study. Alcohol-related problems (eg., social, medical, legal, family, vocational) are assessed on the *Rutgers Alcohol Problem Index* (RAPI) [64], a 23-item self-report measure commonly used in BI studies. Alcohol-related injuries are assessed on the *Extended Adolescent Injury Checklist* (E-AIC) [65]. This 12-item measure records minor and major injuries, whether they required medical attention, and occurred in the context of alcohol or other drug use. The 12-item *University of Rhode Island Change Assessment Scale* (URICA) [66] is used to gauge motivation for changing alcohol use. The 15-item *Controlled Drinking Self-Efficacy Scale* (CDSE) [67], provides a reliable and valid measure of self-efficacy to resist excessive drinking.

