## Statistical analysis

The independent variable is treatment condition, with 3 levels: (i) AF/I; (ii) MI and (iii) PI. The primary outcome variables are alcohol use (TLFB) and related problems (RAPI). Secondary outcomes include mental health symptoms (psychological distress (K10), depression (PHQ-9), social anxiety (Mini Spin), generalised anxiety (GAD-7)), functioning (Social and Role Functioning scales), severity of problematic alcohol use (AUDIT), alcohol-related knowledge, alcohol-related injuries (E-AIC) and coping self-efficacy (CDSE) to resist using alcohol. Preliminary statistical analyses will be undertaken to check for baseline group differences on demographic, primary and secondary outcome variables using one-way analysis of variance (interval data) and chi-square (χ^2^) analyses (categorical data). Intention-to-treat strategies will be used for the main analyses. To determine whether there are group differences on the primary and secondary outcome measures at 1, 3, 6 and 12 months a series of mixed effects model repeated measures analyses of variance (MMRM) will be employed. The within groups factor will be time (baseline, 1, 3, 6 and 12 months) and group will serve as the between subjects factor. This technique can also control for potential confounding variables such as gender, age, injury severity and other drug use.

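### The 1-month RAPI covers 1 month and every other RAPI covers 3, yet all are levels of one time factor; the AUDIT windows also differ, and its screening window is stated two ways

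*Protocol article*

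**What the plan says.** The Statistical analysis section of the protocol article states: "The primary outcome variables are alcohol use (TLFB) and related problems (RAPI". It plans that "a series of mixed effects model repeated measures analyses of variance (MMRM) will be employed" for primary and secondary outcomes, and specifies: "The within groups factor will be time (baseline, 1, 3, 6 and 12 months) and group will serve as the between subjects factor".

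The recall windows are in Table 1 (Measures). The RAPI row is labelled "Rutgers alcohol problem index (RAPI; 3 mths". Its baseline, 3-, 6- and 12-month cells carry a plain mark, so the 3-month label applies to them. The 1-month cell carries its own entry of 1 month. The text under Baseline and follow-up measures calls the RAPI "a 23-item self-report measure commonly used in BI studies" and gives no window, response format or rescaling.

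The row for "Alcohol use disorders identification test (AUDIT" shows 3 months at screening, nothing at baseline, 1 month at the 1-month visit, and 3 months at 3, 6 and 12 months. The text under Screening measures says instead that the AUDIT "screens participants for harmful or problematic drinking in the previous 12 months". Under Eligibility criteria, an AUDIT score of 8 or more is one of two alternative alcohol entry routes. The AUDIT is also a secondary outcome in the same planned model.

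**The concern.** A problem index that asks about the last 3 months and one that asks about the last month need not be on the same scale. If a longer window picks up more problems, the 1-month RAPI is lower than its own baseline, and the 3-month score higher again, with no change in behaviour. With baseline as a level of the time factor, the planned model reads that as change.

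The course of the effect matters here. The Objectives state the hypothesis for each of 1, 3, 6 and 12 months, and the Background remarks that effects of MI tend to wane. On the raw scale the model cannot tell an effect that grows or fades from an effect seen through a different window. The other primary outcome, the TLFB, does not have this problem: apart from screening, its window is about a month at every assessment.

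For the AUDIT, the unresolved screening window affects both an entry route and the only pre-treatment AUDIT value.

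**Working it through.** The plan gives no figure on this point to reproduce. The check sets the windows side by side and then illustrates their effect under stated assumptions.

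**1. Windows (Table 1, with the Screening measures text)**

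| Visit | RAPI | AUDIT | TLFB |
|---|---|---|---|
| Screening | none | 3 months (Table 1) or 12 months (text) | 2 weeks |
| Baseline | 3 months | none | 1 month |
| 1 month | 1 month | 1 month | 1 month |
| 3, 6, 12 months | 3 months | 3 months | 1 month |

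One of the five RAPI levels differs from the rest.

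**2. Apparent change with no true change**

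Let r be the 1-month-window score divided by the 3-month-window score when drinking problems are unchanged. The apparent fall from baseline to 1 month is 1 − r.

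| r (assumed) | Apparent fall |
|---|---|
| 1/3 (score proportional to window) | 67% |
| 0.5 | 50% |
| 0.7 | 30% |
| 1 (window irrelevant) | 0% |

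The article does not give r. As a rough guide, suppose an item is scored yes or no and events arise at a constant rate. An item endorsed with probability p over 3 months is then endorsed with probability 1 − (1 − p)^(1/3) over 1 month. The ratio of the two is 0.345 at p = 0.1 and 0.519 at p = 0.8. This too is an assumption.

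**3. Arm differences on the raw scale**

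Let m be the control mean on the 3-month window and δ the proportional reduction in an active arm. The difference is δ × m at a 3-month-window visit and δ × r × m at month 1.

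- No effect (δ = 0): the difference is 0 at every visit, whatever r is. The window creates neither a between-arm difference nor a group-by-time interaction.
- Constant 20% effect, with m = 9 and r = 1/3 assumed: 0.20 × 3 = 0.6 at 1 month and 0.20 × 9 = 1.8 later. A steady effect looks as if it grows.
- Effect fading from 30% at 1 month to 10% at 3 months, same assumptions: 0.30 × 3 = 0.9 and 0.10 × 9 = 0.9. A real decay disappears.

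**4. Standardised differences**

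Assume overdispersed counts with variance equal to mean + mean², a 25% reduction, and control means of 12 (3-month window) and 4 (1-month window).

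- 3-month window: means 12 and 9, variances 156 and 90, SD = √((156 + 90)/2) = √123 = 11.09. Standardised difference 3.0/11.09 = 0.27.
- 1-month window: means 4 and 3, variances 20 and 12, SD = √((20 + 12)/2) = 4.0. Standardised difference 1.0/4.0 = 0.25.

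The ability to detect an effect at month 1 is barely touched. The raw size and the variance both change with the window.

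**5. AUDIT**

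If the screening window was 3 months, as in Table 1, the screening score matches 3, 6 and 12 months but not month 1. If it was 12 months, as in the text, it matches no follow-up visit. No baseline AUDIT exists to fall back on.

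**The case against.** The strongest reply is that the trial asks about differences between arms at each visit. Every arm has the same window at each visit, and a shift common to all arms goes into the visit mean. This stands. A reader might infer that the 1-month randomised comparison is biased, or that the window alone would produce a group-by-time effect. Steps 3 and 4 show neither.

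The shorter window also has a good reason: a 3-month recall at the 1-month visit would reach mostly into time before baseline and dilute any effect. This stands too. The fault is in treating the score as interchangeable with the others, not in the window.

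A reader might take a 67% fall, or an effect three times smaller at 1 month, as what will happen. Both need scores proportional to the window, and the second also needs the raw scale. The article gives no RAPI scoring format to support that, and nothing that shows how AUDIT scores respond to the window.

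A reader might also infer that the two recruitment sites could apply different AUDIT look-back periods. The Recruitment section has eligibility screened by telephone by trained study assessors, so the article does not support this. The AUDIT window can affect entry only for people who do not qualify by the other route, a recent heavy drinking occasion.

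Finally, an analysis plan that is not shown might handle the 1-month score separately. That is possible, but the article itself states both the unequal windows and the single time factor, so the point concerns what is fixed rather than what is left out.

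**Conclusion.** The point holds in a limited form. For the RAPI, a primary outcome, change from baseline to 1 month and the overall time effect are not like-for-like. When a real treatment effect exists, the raw-scale group-by-time pattern involving month 1 is not like-for-like either. The same applies to the AUDIT at month 1. The between-arm contrast at 1 month remains valid.

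The size is not known from the article. The apparent fall runs from 0% to 67% as r runs from 1 to 1/3. The direction, a lower score at month 1, follows if a longer window captures more problems.

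The AUDIT screening window is a plain contradiction: 3 months in Table 1, 12 months under Screening measures. It matters because the score is one of two alternative entry routes and the only pre-treatment AUDIT value. If 12 months was used, AUDIT change from screening is not like-for-like at any visit.

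**What to change.** For the RAPI and AUDIT models:

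- Enter the pre-treatment score as a covariate, not as a level of the time factor.
- Keep month 1 in the joint model, with its own visit mean, group effect, baseline slope and variance. Removing it would discard the data of participants whose only follow-up is at 1 month, which is unwelcome with 20–30% attrition expected.
- Report month 1 only as a between-arm contrast on its own 1-month scale.
- Base statements about change from baseline, time trend and group-by-time on the 3-month-window visits: 3, 6 and 12 months.

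Separately, reconcile the AUDIT screening window between Table 1 and Screening measures, and state which window was applied. If it was 12 months, use the screening score only as a covariate and make no claim about AUDIT change from screening.

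The cost is a few sentences of analysis wording, a baseline-by-visit term in two models and one corrected AUDIT entry. No extra data are needed. Participants with no follow-up score at all would not enter these models, so the intention-to-treat description should say how they are handled.

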### Screening measures

(i) Demographics: age, gender, occupation, years of education, living arrangements, relationship status, ethnicity.

(ii) Alcohol use: A 2-week *TLFB* uses calendar-based cues to obtain precise information on the frequency and quantity of alcohol use [58]. The 10-item *AUDIT* screens participants for harmful or problematic drinking in the previous 12 months. This well validated measure reliably detects alcohol use disorders in adolescents and adults at a cut-off of ≥ 8 [53].

### Baseline and follow-up measures

(i) Personality risk: The *Substance Use Risk Profile Scale* (SURPS) [60] is a 23-item measure of the level of anxiety sensitivity/proneness (5-items), depression proneness/hopelessness (7-items), impulsivity (5-items), and sensation seeking (6-items) personality risk factors for alcohol abuse or dependence. This scale has high levels of internal consistency, test-retest reliability and construct, concurrent and predictive validity with respect to current and future alcohol use in adolescents, undergraduate students and clinical samples [30,60,61]. It also has high levels of incremental validity (cf. other personality measures) for differentiating reinforcement-specific patterns of drug use [29,60].

(ii) Alcohol and other drug use: *TLFBs* over the previous 4 weeks assess the frequency and quantity of alcohol and other substance use across the study [58]. The *TLFB* method has high test-retest reliability (intraclass correlation coefficients (ICC) = .70-.94), convergent and discriminant validity with other substance use measures, collateral information and biological measures of illicit drug use [58,62]. We found substantial agreement between urine drug screens and self-reported drug use (83%) using the TLFB in a previous study [63]. The age of onset and frequency of alcohol and other drugs use over the previous 12 months is also assessed at baseline.

(iii) Other alcohol outcome measures. Alcohol-related knowledge is assessed using 20 *Alcohol Trivia* questions developed for this study. Alcohol-related problems (eg., social, medical, legal, family, vocational) are assessed on the *Rutgers Alcohol Problem Index* (RAPI) [64], a 23-item self-report measure commonly used in BI studies. Alcohol-related injuries are assessed on the *Extended Adolescent Injury Checklist* (E-AIC) [65]. This 12-item measure records minor and major injuries, whether they required medical attention, and occurred in the context of alcohol or other drug use. The 12-item *University of Rhode Island Change Assessment Scale* (URICA) [66] is used to gauge motivation for changing alcohol use. The 15-item *Controlled Drinking Self-Efficacy Scale* (CDSE) [67], provides a reliable and valid measure of self-efficacy to resist excessive drinking.

(iv) Mental Health: Self-report information on the young person’s history of mental health and substance use disorders, as well as their family history is collected. The *Kessler 10* (K10) [68] is a 10-item self-report measure of psychological distress in the past month. Normative data indicates a cut-off of ≥ 17 is at the 75^th^ percentile among Australian youth [69]. Depression symptoms are measured using the 9-item *Patient Health Questionnaire-9* (PHQ-9) and anxiety symptoms are assessed by the 7-item *Generalised Anxiety Disorder-7* (GAD-7). Social phobia is measured by the 3-item *Mini Social Phobia Inventory* (Mini-SPIN).

(v) Coping and Functioning: Emotion and task-orientated coping are measured with 32-items from the *Coping Inventory for Stressful Situations* (CISS) [70] scale. The clinician-rated *Global Functioning: Social and Role*[71] scales provides two single ratings of the lowest level of social (e.g., peer, family) and role (school, work) functioning in the past month on a 1 (extreme dysfunction) to 10 (superior) scale. Both scales use detailed anchor points for each rating interval and probe questions to increase reliability.

(vi) Cost-Effectiveness: A total health care and personal cost perspective is taken; it does not include costs to society. Health care costs (government, insurers, patients) include the costs of treatment provision (staff costs, missed appointments, record keeping, training, materials, rent and overheads) and exclude research costs. As participants may seek other treatment elsewhere, information on all other health care service use is collected. Service prices are based on standard Australian Medicare and Prescription Benefit Scheme (PBS) schedules. The 20-item *Assessment of Quality of Life-6D* (AQoL-6D) for adolescents provides a measure of health-related quality of life on 6 dimensions (inc. social, mental health, independent living) [72]. It is the only multi-attribute instrument weighted with Australian preference values for use in economic evaluations.

### Treatment satisfaction and fidelity

Treatment satisfaction is assessed at one month follow up using the 8-item *Client Satisfaction Questionnaire-8* (CSQ-8) [73]. MI fidelity is confirmed on the *MITI 3.1.1*[57]. Session Component Checklists are also completed to ensure core features of the allocated treatment are delivered and non-allocated treatments are not delivered.

## Data, safety and risk management strategies

Safety and risk management protocols manage any safety or urgent treatment issues. Young people who are recruited to this study and are subsequently identified as in need of more intensive treatment will be appropriately referred. A clinical trials committee comprised of the authors meets every 3 months to monitor the project’s implementation (inc. study withdrawals), clinical (inc. any serious adverse events) and research (inc. data safety) integrity. Email or telephone consultations are used to determine urgent inclusion or treatment issues, and a record of decision precedents is kept to ensure consistency.

## Statistical analysis

The independent variable is treatment condition, with 3 levels: (i) AF/I; (ii) MI and (iii) PI. The primary outcome variables are alcohol use (TLFB) and related problems (RAPI). Secondary outcomes include mental health symptoms (psychological distress (K10), depression (PHQ-9), social anxiety (Mini Spin), generalised anxiety (GAD-7)), functioning (Social and Role Functioning scales), severity of problematic alcohol use (AUDIT), alcohol-related knowledge, alcohol-related injuries (E-AIC) and coping self-efficacy (CDSE) to resist using alcohol. Preliminary statistical analyses will be undertaken to check for baseline group differences on demographic, primary and secondary outcome variables using one-way analysis of variance (interval data) and chi-square (χ^2^) analyses (categorical data). Intention-to-treat strategies will be used for the main analyses. To determine whether there are group differences on the primary and secondary outcome measures at 1, 3, 6 and 12 months a series of mixed effects model repeated measures analyses of variance (MMRM) will be employed. The within groups factor will be time (baseline, 1, 3, 6 and 12 months) and group will serve as the between subjects factor. This technique can also control for potential confounding variables such as gender, age, injury severity and other drug use.

A two-pronged economic analysis will be conducted. An analysis alongside the trial will display the costs against their benefits in both natural units, such as alcohol-related injuries/illnesses avoided, and QALYs. Costs saved will also be estimated by quantifying visits to GPs and other health service use avoided under the intervention. MI and PI will be assessed against the AF/I arm as comparator. Uncertainty in the assessment will be estimated using non-parametric bootstrapping. In the second modelled CEA, the estimated change in alcohol consumption from the trial will be extrapolated to the general Australian population of 16-25 year olds. The interventions will be evaluated using a model developed for the Assessing Cost-Effectiveness of Prevention (ACE-Prevention) project [74], which determines DALYs averted by an intervention from changes in risk of 20 alcohol-related diseases and injuries. By using this model, we can compare cost-effectiveness of the PI and MI intervention with other alcohol interventions and up to 150 other preventive interventions (e.g., for illicit drugs, obesity, etc.) that have already been evaluated for the Australian population. Data on alcohol-related diseases and injuries from the Australian Burden of Disease 2003 study will be updated to 2015. Links between alcohol consumption and these diseases and injuries are based on the Comparative Risk Assessment study. The model is a multi-cohort, multi-disease model that follows up the target population until death or age 100. Uncertainty will be assessed using a combination of non-parametric bootstrapping for the effect size (alcohol consumption) and Monte Carlo simulation for all other variables (with sampling uncertainty).

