### Sample size calculations

Sample size calculations were generated using SamplePower 3.0. Small to medium effects were anticipated between the three groups (effect size f = .25). This was based on Hides *et al*’s [25] finding of medium-to large effects at 1 (f = -.62), 3 (f = -.51) and 6 months (f = -.47) follow-up between MI and AF/I among young substance users in primary care and Monti *et al’s*[24] finding of small to moderate effects between MI and AF/I at 6 (f = -.24) and 12 (f = -.33) months follow-up in young alcohol users recruited from an ED. With power set at 0.95 and α to .05, 82 cases per group, or a total sample of 246 is required. We predict a 20-30% attrition rate based on our previous work and will therefore recruit a total of 390 participants over 18 months. With 82 young people in each group, we will have 88% power to detect small to moderate effects for the planned three group comparisons. Nevertheless, all young people will be included in the intent-to-treat analysis.

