### Randomization

An independent statistician generated a computerised random number sequence stratified by gender and age (16-20 years, 21-25 years), incorporating permuted blocks (blocks of 3 and 6) to allocate participants to one of three treatment groups (i) MI; (ii) PI or (iii) AF/I (Figure 1) [55]. The randomization sequence is concealed within a secure database, only accessible to the trial manager, who logs in to allocate participants when a baseline assessment is completed. The chief investigators, follow-up assessors and trial statistician are all blind to treatment group allocation.

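### Baseline is a level of the time factor with no stated adjustment, and the stratification factors are only optional covariates: an avoidable loss of precision, not a bias

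*Protocol article*

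**What the plan says.** The Statistical analysis section gives its aim as finding group differences on the primary and secondary outcomes at 1, 3, 6 and 12 months, using a series of mixed-model repeated-measures analyses. The factors are then fixed: "The within groups factor will be time (baseline, 1, 3, 6 and 12 months) and group will serve as the between subjects factor". Baseline is therefore one of five response levels. The section does not mention a baseline covariate or an equal-baseline constraint.

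On covariates, it says: "This technique can also control for potential confounding variables such as gender, age, injury severity and other drug use". The verb is permissive and the list is open. The Randomization section says that the sequence is "stratified by gender and age (16-20 years, 21-25 years"), so two of the listed examples are design variables.

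Before the main models, one-way ANOVA and chi-square tests will "check for baseline group differences on demographic, primary and secondary outcome variables". The section states no consequence of these tests.

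**The concern.** In a randomised trial the arms have the same expected baseline. An efficient model uses that fact, either by conditioning on the baseline value or by giving all arms one baseline mean. A group-by-time model with baseline as an ordinary time level, as usually fitted, estimates a separate baseline mean in each arm and so gives this information away. The analyst then has two natural contrasts: the group difference at a visit, which does not use baseline, or the difference in change from baseline, which subtracts all of baseline when only part of it predicts the outcome. Both have larger variance than a baseline-adjusted contrast.

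Stratified randomisation makes the arms more alike on gender and age band. If the model omits these factors, its standard errors do not reflect that balance and are too large to the extent that the factors predict drinking or alcohol problems.

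What is at stake is the width of the confidence intervals on both primary outcomes, TLFB alcohol use and RAPI, in a trial with three active arms.

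**Working it through.** **Inputs from the protocol** (Sample size calculations)
- "Small to medium effects were anticipated between the three groups (effect size f = .25"). For a two-group contrast, f = 0.25 corresponds to d = 2f = 0.5 SD.
- "With power set at 0.95 and α to .05, 82 cases per group, or a total sample of 246 is required".
- "we will have 88% power to detect small to moderate effects for the planned three group comparisons".
- "We predict a 20-30% attrition rate based on our previous work and will therefore recruit a total of 390 participants over 18 months".

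**Assumptions, not in the protocol**
- Correlation r between baseline and follow-up, taken as 0.3, 0.5 and 0.7. The TLFB test-retest coefficients in the Measures section are reliability figures and do not supply r.
- Equal variance at all visits (set to 1), the same r between any two visits, complete data, and two-sided alpha of 0.05.

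**Step 1. Reproduce the plan's figures.** One-way ANOVA with three groups, 82 per group and noncentrality N·f² = 246 × 0.0625 = 15.375 gives 94.7% power. Strict 95% needs 84 per group, so 82 is close enough. A two-group comparison at d = 0.5 with 82 per group gives 88.9%, which matches the stated 88%. The plan's power therefore takes no credit for baseline.

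**Step 2. Variance of a group contrast at one visit**, in units of 2/n:
- visit difference, no baseline: 1
- change from baseline: 2(1 − r)
- baseline-adjusted (baseline as covariate, or common baseline mean): 1 − r²

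Ratios to the adjusted contrast are 1/(1 − r²) for the visit difference and 2(1 − r)/(1 − r²) = 2/(1 + r) for change. A generalised least squares calculation with five visits gave the same ratios, and the common-mean model matched the baseline-covariate model exactly.

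| r | visit | change | adjusted | visit / adjusted | change / adjusted |
|---|---|---|---|---|---|
| 0.3 | 1 | 1.40 | 0.91 | 1.10 | 1.54 |
| 0.5 | 1 | 1.00 | 0.75 | 1.33 | 1.33 |
| 0.7 | 1 | 0.60 | 0.51 | 1.96 | 1.18 |

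Adjustment beats the change contrast for every r below 1 and the visit difference for every non-zero r.

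**Step 3. Power at 82 per group, d = 0.5**, using noncentral t with effect 0.5/√(variance factor):

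| r | visit | change | adjusted |
|---|---|---|---|
| 0.3 | 88.9% | 76.7% | 91.6% |
| 0.5 | 88.9% | 88.9% | 95.7% |
| 0.7 | 88.9% | 98.4% | 99.4% |

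**Step 4. Allow for recruitment beyond 246.** With 30% attrition, 390 × 0.7 / 3 = 91 per arm. At d = 0.5 the visit difference has 91.8% power whatever r is. At r = 0.5 the change contrast also has 91.8%, and the adjusted contrast 97.2%. At r = 0.3 the change contrast has 80.9%, against 94.0% adjusted.

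**Stratification.** No figure can be given. The gain depends on how strongly gender and age band predict the outcomes, which the protocol does not say.

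**The case against.** The best defence has four parts.

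*The sentence does not exclude an efficient model.* Baseline as a response is also the starting point of the common-mean model, and the choice between free and common means is often left to an analysis plan, which is not shown here. This is fair, and is why the point is conditional on the ordinary reading. But the article gives the factors of the model explicitly, and a reader who fits them as written gets free means.

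*The sample size does not rely on adjustment.* True. The stated 88% reproduces without it, and the recruitment target leaves a margin. The trial is not underpowered on its own terms because of this; it forgoes precision it could have.

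*The covariate list may be closed elsewhere.* Also fair, so this part is weaker than the baseline part. Omitting the strata errs on the conservative side.

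*Stronger readings go beyond the text.* A reader might infer that the deciding test is a group main effect diluted by the baseline visit, or an interaction test across all five time points. The article names neither as decisive; its stated aim is differences at the four follow-up visits. A reader might also infer that baseline p-values will select the covariates. The tests come before an optional list, which leaves room for that, but no sentence links them. Nor does the article plan to adjust for drug use measured after randomisation: it lists other drug use as a potential confounder, and a baseline record exists. None of these is part of the finding.

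**Conclusion.** The point holds as a loss of efficiency under the ordinary reading of the stated model. For r between 0.3 and 0.7, the unadjusted contrasts have between 10% and 96% more variance than the adjusted one, depending on r and on which contrast is reported. At r = 0.5, 82 per group and 0.5 SD, this is 89% against 96% power. These sizes rest on an assumed correlation, equal variances and complete data; the direction does not depend on the value of r within that range. The treatment estimates are not biased by this choice, and nothing here shows the planned sample to be inadequate. It is a worthwhile improvement to the analysis wording rather than a fault that threatens the trial's conclusions.

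**What to change.** State one of two equivalent models for each continuous outcome measured at baseline:

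1. Outcomes at 1, 3, 6 and 12 months (those at which the outcome is scheduled) as the response, with group, visit, group by visit, the baseline value, gender and age stratum (16-20, 21-25) as fixed terms.
2. Baseline kept as a response with one mean common to all three arms, plus gender and age stratum. This form also keeps participants who have only a baseline record.

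Report the group contrasts at the stated visits from that model. Name gender and age stratum as terms that are always included, and state that the baseline significance tests do not decide which covariates enter; a descriptive baseline table would serve the same purpose.

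The cost is a few sentences of analysis wording. Every variable is already collected, and sample size, visits and procedures are unchanged.
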